### Allocation

Randomization follows a 3-arm, type 2-2-1 (“toxin,” “baclofen,” and “placebo”) design. This process is conducted by Creapharm, the manufacturer and packager of the protocol’s therapeutic batches. Creapharm is an independent company approved by the French drug agency (ANSM). Each center receives therapeutic batches containing 5 treatment packages (2-2-1). Randomization is therefore stratified by center.

A copy of the randomization list is kept by Creapharm and the sponsor’s pharmacy. Randomization is performed before the study starts by assigning an inclusion number in the protocol that aligns with a specific therapeutic batch number. The pharmacy in each center is responsible for accurately assigning the therapeutic batch number associated with the inclusion number. This detail is routinely verified by the principal investigator at each center.

### Blinding

Participants, care providers, investigators, outcome assessors, the data manager, and the biostatistician are blinded to the assignment of the intervention. The blind will be lifted after the statistical analyses**.**

During the research, the investigator and the sponsor can request unblinding if necessary, with the agreement of the coordinating investigator. Unblinding might be necessary in case of a serious, life-threatening AE. Otherwise, unblinding only occurs after the database has been finalized at the end of the research.

In this study, a 2-2-1 randomization scheme is used, resulting in 2 treatment groups and 1 placebo group with differing sample sizes. While blinding is strictly maintained for the 2 treatment groups, the smaller size of the placebo group could potentially reveal its identity during data analysis. To minimize bias and preserve blinding integrity, all data analyses will be conducted on coded datasets, with each group labeled as “group 1,” “group 2,” or “group 3,” without specifying treatment identities. This approach ensures that data handling and interpretation are unbiased until the final analysis is complete. Additionally, the randomization and allocation processes are managed independently by a third-party data manager who has no role in data collection or analysis. These measures aim to uphold objectivity and reduce any influence of group size on the interpretation of results.

### Data Collection and Management

All personnel involved in data collection undergo training before the study begins. The data are routinely collected in the management of patients post stroke.

Participants are informed that there will be additional tests during the close-out visit (V3) following the treatment. Moreover, there is a sincere desire among participants to receive the treatment for an adequate duration. Any discontinuation or deviation from the study protocol is documented along with the reasons for discontinuation.

All the information mandated by the protocol is documented in observation logbooks, with explanations provided for any missing data. Data should be recorded promptly and transcribed neatly into the logbooks. If any erroneous data are identified, it should be clearly crossed out and the correct information entered along with the initials, date, and justification by the investigator or the authorized person who made the correction. These records are maintained in paper observation logbooks with 2 copies generated. One copy is kept by the center investigator, while the second is kept by the research monitor after monitoring. Laboratory and clinical examination results are clearly entered in the clinical records, and scales, which are considered source data, are entered directly in the observation logbooks.

Data are entered on paper by the research technician at each center and electronically at the coordinating center. One copy of the observation logbook triplicate is sent to the coordinating center. The clinical research technician at the coordinating center verifies the accuracy of data and validates the computerized data. Data validation aligns with the data management plan developed by the coordinating investigator and the Methodology and Data Management Centre, which comprises a methodologist, a data manager, and a statistician.

The process of freezing or unfreezing data follows the established procedure at the Methodology and Data Management Centre where raw data are frozen in XML format and as an SAS (version 9.4; SAS Institute) table. Daily backups of the dataset are kept for 4 weeks, followed by monthly tape-recorded archiving.

MéDatAS-CIC is a methodology, data management, and biostatistics center to which the sponsor is affiliated, and which acts as a research support team. The Clinical Investigation Centre is responsible for coordinating the conduct of the study. This service is funded by the Programme Hospitalier de Recherche Clinique (PHRC) grant.

### AE Reporting

The investigator was required to promptly notify the sponsor of any serious AEs (SAEs) or significant developments, occurring at any time from the date of informed consent signing, throughout the patient’s scheduled follow-up, and up to 30 days after follow-up completion if the event was likely related to the research. SAEs are defined as events resulting in death, life-threatening situations, hospitalization or prolongation of existing hospitalization, significant or permanent disability, or interventions to prevent such outcomes. Minor AEs are defined as medical occurrences not meeting SAE criteria but which may still relate to study procedures. The sponsor is then responsible for timely reporting of unexpected SAEs and other new occurrences to the ANSM and the relevant ethics committee.

In cases where participants may have been affected, the ethics committee will ensure that the participants are informed of relevant AEs and confirm their ongoing consent.

### Statistical Methods

#### Statistical Methods for Primary and Secondary Outcomes

The baseline characteristics of the participants are described for the 3 treatment groups and the pairwise standardized differences are used to compare the distribution of baseline covariates between treatment groups.

The variation in the Fugl-Meyer score between the “toxin” and “baclofen” groups is compared using linear regression models. First, the model contains the treatment group as the explanatory variable and the Fugl-Meyer delta score as the response variable. The adjusted model then incorporates the patient’s age, the center, and any associated treatment as explanatory variables, in addition to treatment. The associated treatment is represented by a binary variable indicating the use of at least 1 serotonin reuptake-inhibiting antidepressant (yes or no) or at least 1 benzodiazepine (yes or no). This list is validated during the descriptive analysis of concomitant treatment.

The primary objective tests the superiority of the “toxin” versus “baclofen” in motor recovery at 3 months using 2-sided tests at a 5% α level. The secondary objective aims to demonstrate the clinical equivalence of the “toxin” versus the “placebo” in motor recovery after 3 months, using a 1-sided noninferiority test at a 5% α level and a margin of 13 FMA points to assess noninferiority.

To assess the efficacy of these treatments on spastic symptoms (MAS, Tardieu angle, and Tardieu Scale), 2-tailed *t* tests at a significance level of 5% are conducted for pairwise comparisons. The first analysis is carried out on all muscle groups, and a second analysis is carried out on the muscle groups that have been injected.

For the FMA at 1 month and the variation score between allocation and the second postallocation visit which consists of the RMA the Barthel Index, the Rankin score, the reaction time, satisfaction, pain, and the RNLI, the analyses will be descriptive using the usual statistical measures in each group with a 95% CI.

The modified intention-to-treat population consists of all randomized participants who meet the inclusion criteria, having taken at least 1 dose of the study treatment, and with at least 1 postrandomization evaluation. The per-protocol population includes all patients who complete the study as specified in the protocol, excluding those who do not meet the inclusion criteria, for whom there are major protocol deviations during follow-up, or who do not adhere to the treatment regimen as per protocol. The safety analysis population includes all randomized participants who received at least 1 dose of the study treatment. The modified intention-to-treat population is used to analyze all study objectives. Only the secondary objective, which assesses the noninferiority between the “toxin” and the “placebo is analyzed in the per-protocol population, while AEs are analyzed in the safety population. All statistical analyses are conducted in SAS.

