### Objectives

#### Main Objective

This study aims to demonstrate the superiority of botulinum toxin A over baclofen on motor recovery in the subacute phase after stroke. The primary end point is the change in the Fugl-Meyer Assessment (FMA) motor score from the start of treatment to 3 months later.

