### Sample Size

The study includes three arms as follows: (1) the “toxin” group, which receives an injection of botulinum toxin and placebo oral baclofen; (2) the “baclofen” group, which receives oral baclofen and an injection of placebo botulinum toxin; and (3) the “placebo” group, which receives placebo oral baclofen and an injection of placebo botulinum toxin. All groups receive standard neurorehabilitation care.

This study is a randomized parallel 2-2-1 type design, which corresponds to the “toxin,” “baclofen,” and “placebo” groups, respectively. The main objective, which is to demonstrate the superiority of “toxin” over “baclofen” on motor function, corresponds to a 2-2 comparison. The secondary objective, which is to demonstrate the noninferiority of “toxin” to “placebo” on motor function, corresponds to a 2-1 comparison. The “placebo” arm is limited due to ethical considerations.

The sample size for the “toxin” and “baclofen” arms was calculated with the 2-sided test at a 5% significance level. This analysis compared the superiority of the toxin over baclofen indicated by the FMA gain, between the allocation visit (V0) and the second postallocation visit (V2). The expected variation in FMA was estimated at 30 points between V0 and V2. [35]. For an 85% power and an FMA difference of 12 points between the “toxin” and “baclofen” groups, 120 patients per group were initially required, accounting for missing data and protocol deviations. This 12-point difference was based on the minimal clinically important difference of FMA, which was approximately 6 points for both the upper [36] and lower extremities [37]. Doubling the minimal clinically important difference for a total FMA score ensured a clinically significant change.

To demonstrate equivalence between the “toxin” and “placebo” groups, a 12-point unilateral zone of equivalence was defined. With an SD of 30 points, 60 patients in the “placebo” arm yielded a power of approximately 80% (77.6%), accounting for 10% missing data.

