#### Methods for Additional Analyses (eg, Subgroup Analyses)

The proportional recovery rule serves as a predictive model for understanding poststroke recovery. It examines the correlation between initial impairment and subsequent recovery by analyzing FMA-UE both at baseline and in follow-up sessions and defines recovery as the change over time [38]. This research suggests that, on average, a significant subset of patients typically regains approximately 70% of their maximum potential recovery from impairment, while a smaller subgroup experiences notably less recovery. For recovery to be considered proportional, patients must recover roughly 70% of their maximum possible potential at the 3-month mark [38]. Patients who initially show mild to moderate deficits according to the FMA-UE (>10) at baseline often follow a pattern known as “recoverers” [39,40]. Those who display a proportional recovery profile tend to have corticospinal tracts that are less affected throughout the entire course [40,41].

Identifying participants with a proportional recovery profile based on the initial FMA-UE seems to be a promising method for participants with stroke, allowing for a more accurate assessment of treatment effectiveness [42]. This subgroup analysis helps to avoid missing treatment effects within the larger group by focusing on those with a “recoverers” profile.

These groups are determined based on whether the FMA-UE is greater than or equal to 11 or strictly less than 11 during the allocation visit [40].

Within the “recoverers” and “nonrecoverers” groups, linear regression models are used in a comparative analysis between the “toxin” and “baclofen” groups regarding the variation in the FMA-UE score. Initially, an unadjusted analysis uses treatment as the sole explanatory variable and the FMA-UE delta score as the response variable. The adjusted model incorporates the patient’s age, the center, and the presence of associated treatment as explanatory variables, in addition to treatment.

The same unadjusted and adjusted models are also computed using the FMA-LE as the response variable in both the “recoverers and the nonrecoverers” groups.

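### Neither fixed model for the primary FMA change includes baseline FMA, and the article does not say which of the two carries the 5% test

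*Protocol article*

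**What the plan says.** The Main Objective section of the protocol article defines the primary endpoint as "the change in the Fugl-Meyer Assessment (FMA) motor score from the start of treatment to 3 months later". Statistical Methods for Primary and Secondary Outcomes sets out two linear regressions for toxin against baclofen. In the first, "the model contains the treatment group as the explanatory variable and the Fugl-Meyer delta score as the response variable". For the second: "The adjusted model then incorporates the patient’s age, the center, and any associated treatment as explanatory variables, in addition to treatment". The V0 FMA is in neither list. The same section then tests superiority "using 2-sided tests at a 5% α level" without saying which regression supplies that test. The Abstract mentions only regression adjusted for covariates of the same kind.

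Two other sections bear on this. Allocation says: "Randomization is therefore stratified by center". Methods for Additional Analyses introduces the proportional recovery rule: "It examines the correlation between initial impairment and subsequent recovery by analyzing FMA-UE both at baseline and in follow-up sessions". The baseline FMA-UE is then used only to split patients at 11 points. Within each subgroup the same pair of models is repeated for FMA-UE and FMA-LE, again without the baseline score.

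**The concern.** Subtracting the baseline removes the influence of a chance baseline difference only if change itself is unrelated to baseline. The article argues that it is related: patients with milder initial deficits tend to regain a roughly fixed share of what they lost, and a smaller group regains notably less. A variable that the plan itself treats as prognostic therefore stays in the error term. This happens in a trial that randomized 179 patients against a reduced target of 214, so precision cannot be bought with more recruitment. The treatment-only model also leaves out center, the stratification factor.

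The second issue is what counts as the primary result. Two models address one hypothesis at one significance level. If they fall on opposite sides of 5%, the article gives no rule for reading the trial.

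**Working it through.** **Inputs.** Two-sided 5% (Sample Size: "was calculated with the 2-sided test at a 5% significance level"); difference 13 points (amended target); SD 30; 10% data loss; 2:2:1 allocation; 179 randomized (Results). The article calls 30 an SD only for the placebo comparison. That reading reproduces its figure: with 108 v 54 patients (120 and 60 less 10%) and margin 12, SE = 30 × √(1/108 + 1/54) = 5.00, and Φ(12/5.00 − 1.645) = 77.5%, against 77.6% stated.

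**The plan's own size for the primary comparison.** With 85% power (stated for the 12-point design and not restated for the amendment), n = 2 × (1.960 + 1.036)² × 30²/13² = 96 per arm, or 107 after 10% loss. The stated 85 is not reproduced. With 76 analyzed (85 × 0.9 = 76.5, rounded down), power is 76.2%. That discrepancy is a separate matter; it is shown because it sets the starting level of power.

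**Effect of adding baseline FMA.** Residual SD = 30 × √(1 − c²), where c is the correlation between baseline FMA and FMA change. The documents give no value for c, so the range is an assumption. Power = Φ(13 / (SD × √(2/n)) − 1.960). The realized active-arm size is 179 × 2/5 = 71.6, or 64.4 after an assumed 10% loss.

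| c | Residual SD | Power, 64.4 per arm | Power, 71.6 per arm |
|---|---|---|---|
| 0 (baseline omitted) | 30.0 | 69.1% | 73.7% |
| 0.1 | 29.9 | 69.6% | 74.1% |
| 0.3 | 28.6 | 73.2% | 77.6% |
| 0.5 | 26.0 | 81.1% | 84.9% |

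The gain therefore runs from under 1 point to about 12 points. The formula ignores the degrees of freedom spent on 18 center terms.

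**Two models, one test.** Suppose, for the calculation only, that a p value below 0.05 in either model could be claimed. For two normal test statistics the error rate is 5.7% at correlation 0.99, 6.5% at 0.95 and 7.0% at 0.90; independent tests would give 9.75%. Simulations with 64 per arm and centers balanced between arms, under no effect, gave:

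- center alone explaining 10–30% of variance: 5.0–5.5%;
- 10% explained, split equally between center and age: about 5.6–5.8%;
- 30% explained, split equally: about 6.3–6.6%.

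**The case against.** **The comparison is valid as planned.** A reader might infer that omitting baseline biases the treatment effect. It does not: under randomization the change-score comparison is unbiased on average. Only efficiency and robustness to chance imbalance are lost.

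**The correlation may be small.** A reader might take 0.3 to 0.5 as established, or baseline FMA as the strongest prognostic factor. The documents say neither, and the recovery rule is described for FMA-UE, not for total FMA. The mix it describes can flatten the linear relation: recoverers gain less in points the milder they start, while the most impaired are often those who gain little. In illustrative mixtures (30–60% nonrecoverers regaining 10–30% of the deficit) the linear correlation ran from −0.27 to +0.33. This objection stands against baseline FMA as the only added term. It is weaker once the FMA-UE stratum is included. With nonrecoverers at 20–65%, regaining 15% of the deficit against 70% in recoverers, and noise SD 10–20, baseline alone explained 0–5% of the variance in change, and baseline plus stratum 14–50%. These inputs are invented for illustration, and a clean split at 11 is the favorable case.

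**The unadjusted model is the natural primary.** It is presented first, in the main and the subgroup analyses, and the sample size uses no covariates. The Abstract, however, describes the adjusted analysis. The hints conflict and no sentence settles it.

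**Error inflation is easily overstated.** Treating all covariates as left to chance gives 6.5–7.6% when they explain 10–30% of variance. That ignores the balance by center, and no sentence says that success in either model would be enough.

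**Some of this could sit in the SAP.** A label for the deciding model could. The covariate lists could not be excused that way, because the article itself fixes them.

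**Conclusion.** The point holds as one of efficiency and clarity, not validity. Both covariate lists are fixed without baseline FMA, against the article's own prognostic reasoning, although the score is already collected. The size of the loss is uncertain: at about 64 per active arm, negligible if the baseline-change correlation is near 0.1, about 4 power points at 0.3 and 12 at 0.5. These figures assume SD 30, a 13-point effect and, for the 69% starting value, 10% loss; without loss the starting value is about 74%.

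The unnamed deciding model is real but secondary. Its consequence is an undefined reading when the models disagree. Any inflation of the 5% level is about 0 to 2 points, and arises only if either result were allowed to count.

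**What to change.** Before unblinding, name one primary model for toxin v baclofen: FMA change (or V2 FMA, which gives the same treatment estimate once baseline is in the model) on treatment, baseline total FMA, baseline FMA-UE stratum (11 or above v below 11), center and age. State that this model alone carries the two-sided 5% test, and label the treatment-only model a sensitivity analysis.

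Associated treatment is left out of this model openly. The article does not say whether its use is measured before or after randomization, and its list is to be settled during the descriptive analysis. It can stay in a supportive model.

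Add the matching baseline score to the FMA-UE and FMA-LE subgroup models, where the stratum term drops out. Use the same primary model for toxin v placebo. The outcomes that the plan only describes or compares by t test need no change on this account.

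The cost is a short dated paragraph and no new data. The article plans to analyze coded groups before the blind is lifted, so the choice should be recorded before the first outcome analysis, even a coded one. The article reports that none had been run by December 2024; whether that is still so cannot be told from it.

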#### Permitted Care During the Trial

Certain medications could impact motor recovery, particularly GABAergic treatments, which were closely monitored. Patients already on a long-term prescription (over 1 month) of sleeping or anxiolytic treatment might continue this treatment. Discontinuing these patients’ medications had more drawbacks than benefits. Zolpidem and zopiclone, commonly prescribed to patients with poststroke sleep disorders, were permitted during this trial.

Considering the prevalence of poststroke depression and its influence on functional recovery, specific antidepressants are authorized. Antidepressants in the serotonin reuptake inhibitor class were permitted. These medications could potentially facilitate motor recovery irrespective of their antidepressant properties [23]. However, randomization aimed to evenly distribute these treatments across all groups, which minimized the risk of bias.

For secondary stroke prevention, patients were administered treatment according to current recommendations (antiplatelet agents, antihypertensive agents, and cholesterol-lowering agents). Effective-dose anticoagulants (heparin and anti–vitamin-K) were grounds for noninclusion due to the risk of muscle hematoma during injections. However, if necessary, during the protocol postinjection, effective-dose anticoagulants were prescribed without necessitating withdrawal from the study.

It is important to note that all patients received standardized functional neurorehabilitation for 2 hours daily, which included physiotherapy and occupational therapy sessions in line with current practices.

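### The adjusted model for the primary outcome uses a drug-use covariate that is not limited to use at allocation, so it can condition on use affected by treatment; its single flag also joins drugs with opposite expected effects

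*Protocol article*

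**What the plan says.** Under Statistical Methods for Primary and Secondary Outcomes, the Protocol article compares the FMA change between toxin and baclofen with two linear models. "First, the model contains the treatment group as the explanatory variable", with nothing else in it. The adjusted model then adds age, "the center, and any associated treatment as explanatory variables, in addition to treatment". Neither model is named as the primary analysis.

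The associated-treatment covariate is "represented by a binary variable indicating the use of at least 1 serotonin reuptake-inhibiting antidepressant (yes or no) or at least 1 benzodiazepine". On how the drugs are settled, the text says: "This list is validated during the descriptive analysis of concomitant treatment". It gives no time window for use.

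Methods for Additional Analyses carries the covariate into the adjusted models for recoverers and nonrecoverers, as "the presence of associated treatment as explanatory variables, in addition to treatment".

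Permitted Care During the Trial explains why these drugs matter: "Certain medications could impact motor recovery, particularly GABAergic treatments, which were closely monitored". Of the antidepressants it says "Antidepressants in the serotonin reuptake inhibitor class were permitted", and adds: "These medications could potentially facilitate motor recovery irrespective of their antidepressant properties". The same section allows zolpidem and zopiclone, lets patients on long-term sleeping or anxiolytic drugs continue them, and relies on randomization to spread such treatments evenly. Prohibited Care During the Trial bars anxiolytics and other benzodiazepines apart from zolpidem or zopiclone. The Background section states that GABAergic agents such as diazepam can impair recovery.

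**The concern.** A covariate recorded before randomization can be adjusted for safely. One that the randomized treatment may change cannot. Here the covariate is drug use with no baseline limit, and some of the drugs concerned may be started during follow-up. The protocol anticipates sedation during baclofen escalation and monitors somnolence and fatigue, so the arms could plausibly come to differ in antidepressant or hypnotic use. Conditioning on such use can remove part of the treatment effect, or create an association between arm and prognosis that randomization had excluded. What is at stake is the adjusted toxin-baclofen estimate, overall and in the two recovery subgroups.

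Two further features weaken the covariate. Its list is confirmed after the trial's own medication data have been described. And one yes/no flag combines a class expected to help recovery with a class expected to hinder it, so it does not address the reason for adjusting.

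**Working it through.** **1. Can the covariate include use after randomization?** The methods text speaks of use and of concomitant treatment, without restricting either to V0. SSRIs and zolpidem or zopiclone are allowed during the trial. Read as written, the covariate can therefore include later starts. Randomization balances use that precedes it or is unaffected by treatment; it gives no assurance about use that treatment changes.

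**2. Size.** The documents give no figure for this covariate, so there is none to reproduce. In a least-squares model with treatment and one flag,

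adjusted estimate = unadjusted estimate − γ × (p_tox − p_bac),

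where γ is the coefficient of the flag and p the proportion flagged in each arm. A simple illustration with assumed figures: a 15-percentage-point difference in use and a 10-point association give 0.15 × 10 = 1.5 FMA points. That is 1.5/13 = 12% of the target difference and 1.5/30 = 5% of the SD.

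**3. Illustrative simulation** (2,000,000 patients per scenario). From the Sample Size section: a 13-point effect and an SD near 30. Assumed: 40% SSRI and 20% benzodiazepine use at average prognosis in the toxin arm, and a prognostic factor worth 15 FMA points per SD. In every row but the first, poorer prognosis raises the log-odds of use by 1 per SD. The drugs have no effect on FMA except in row 2, where the effects are +6 (SSRI) and −6 (benzodiazepine).

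| Assumed effect of baclofen on use (log-odds) | Flagged, toxin / baclofen | γ | Unadjusted | Single flag | Two indicators |
|---|---|---|---|---|---|
| None, use unrelated to prognosis | 52% / 52% | −0.06 | 12.96 | 12.96 | 12.96 |
| None, drug effects +6 and −6 | 52% / 52% | −11.77 | 12.97 | 12.96 | 12.97 |
| SSRI +0.5 | 52% / 60% | −13.83 | 12.99 | 11.90 | 11.86 |
| SSRI +1 | 52% / 68% | −13.85 | 12.99 | 10.80 | 10.75 |
| Both +1 | 52% / 74% | −14.21 | 12.95 | 9.87 | 8.80 |
| SSRI −1 | 52% / 39% | −13.73 | 13.07 | 14.86 | 15.06 |

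Check of the fourth row by the formula: 12.99 − (−13.85) × (0.52 − 0.68) = 12.99 − 2.22 = 10.77, which agrees with 10.80 apart from rounding of the proportions.

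The table shows three things. Without an arm effect on use there is no bias, even when use is tied to prognosis. With one, the single-flag estimate is off by about −3 to +2 points. Two separate indicators do not remove that bias, so it comes from conditioning on use affected by treatment and not from merging the classes.

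**4. What merging does.** Take drug effects of +6 and −6, independent use at 40% and 20%, and no link to prognosis. The proportion flagged is 1 − 0.6 × 0.8 = 0.52. The mean drug effect among flagged patients is (6 × 0.40 − 6 × 0.20)/0.52 = 1.2/0.52 = 2.3; among the unflagged it is 0. The simulated coefficient is also +2.3, and separate indicators return +6.0 and −6.0. With equal use of the two classes the merged value would be 0.

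**The case against.** The strongest reply is that the main comparison is protected. The treatment-only model is fitted first and this covariate does not enter it. A reader might infer that the trial's primary estimate is compromised; the article does not support that, because it does not designate the adjusted model as primary. This stands, and it confines the point to the adjusted models.

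Second, use during the trial is inferred. The article states no window, and a fuller plan might set one. The inference rests on the word concomitant and on the drugs being allowed during the trial. The benzodiazepine part is also largely pre-existing: new use is barred except for zolpidem and zopiclone, and the text does not say whether those count as benzodiazepines for this covariate. The exposure is therefore mainly newly started SSRIs, plus those hypnotics if counted. That narrows the concern without removing it.

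Third, a reader might infer that the covariate is invented after seeing the data. That goes too far. Both classes and the yes/no coding are named in advance, only the list is validated at the descriptive stage, and under Blinding the analysis runs on coded groups with a blinded biostatistician. Some data-dependent choice remains.

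Fourth, yes or no appears after each class, which could describe two variables. The reference to a single binary variable, and to the presence of associated treatment in the subgroup models, favours one.

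**Conclusion.** The point holds for the adjusted model of the FMA change and for the adjusted subgroup models. As written, they can condition on drug use that follows randomization. If treatment changes that use, the adjusted toxin-baclofen estimate is biased, in a direction and by an amount that the documents do not determine. The range of 9.9 to 14.9 around 13 rests on assumed rates of use, an assumed prognostic effect and an assumed shift by arm. It shows what is possible, not what is expected, and nothing in the documents says that use differs by arm.

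Two stronger statements should be avoided. Merging the classes does not itself bias the treatment effect. Nor does opposition of the effects mean that the flag adjusts for nothing: the coefficient cancels fully only when use of the two classes is also similar. What can be said is that the single flag is largely uninformative about the drug effects it is meant to capture. This is a cheap improvement to a companion analysis.

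**What to change.** In the adjusted models for the primary outcome and for the subgroups, define associated treatment as use at V0, with two separate indicators: SSRI (yes/no), and benzodiazepine or other GABAergic hypnotic or anxiolytic (yes/no). Fix the drug list before the data are viewed. Alternatively, drop the term. Describe drugs started after V0 by arm, without adjusting for them.

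The permitted-care and prohibited-care sections differ on continued long-term anxiolytics. They must be reconciled, because this affects who counts as a user.

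The cost is a change of wording. It requires that medication status at V0 can be identified in the records, and it gives up adjustment for later use. According to the Results section, no analysis had been done by December 2024 and the database was not yet frozen, so on the article's account the change could be made before results were seen.
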